## 14.3. Interim analysis

No interim analyses are planned.

## 14.4. Patient Populations for Analysis

The following analysis populations will be defined for this study:

**Randomized:** will include any patient randomized into the study. This population can be referred to as the Intent-to-Treat population.

**Full Analysis:** will include any patient randomized into the study that receive a dose of study drug and have post-baseline polysomnography data. This analysis population may also be referred to as the modified Intent-To-Treat population.

**Safety:** Any patient randomized into the study that receives a dose of study drug.

**Per-Protocol:** Any patient who is randomized and receives the protocol required study drug exposure and required protocol processing, e.g., patients who undergo all five overnight visits [Nights 1, 8, 22, 29 ( $\pm 2$  days) and 36] in which PSG is assessed.

Primary analyses of efficacy endpoints (primary and secondary) will be performed on the Full Analysis Set. Additionally, these analyses will be repeated on the Per-Protocol set. Safety summaries will be based on Safety set. Patient characteristics will be presented for all patients randomized.

#### **14.5. Pooling of Centers**

Low enrolling sites will be pooled for analysis and the pooling algorithm will be determined prior to breaking the blind. The goal of pooling low enrolling sites is to have a sufficient number of patients per treatment group within site for the analysis models and for the evaluation of the treatment-by-site interaction for the primary endpoint. Unless otherwise specified, the pooled sites will only be used in the analyses where site is an effect. The actual sites rather than the pooled sites will be specified in data listings.

#### **14.6. Demography and Other Baseline Data**

Demographic data and patient characteristics at screening/baseline will be listed and summarized by treatment group for all randomized patients using descriptive statistics.

Analysis will be conducted to determine differences of the treatment groups in the demographic characteristics. Baseline comparability will be evaluated based on the pooled data from all centers. To determine comparability of the treatment groups at baseline, continuous demographic and clinical variables will be analyzed by an ANOVA model that includes a main effect for treatment, those that are ordinal by the Mantel-Haenszel test, and those that are dichotomous by the chi-square test or Fisher's exact test. If there is treatment group differences at the 0.10 level of significance in demographic or baseline clinical variables, these variables may be added as stratification variables or covariates to the efficacy analyses (will be considered as exploratory sensitivity analyses only).

Medical history (medical conditions ending prior to start of study medication) will be summarized treatment group using the system organ class (SOC). Refer to section 13.10.1 for details

Deviations from inclusion/exclusion criteria as well as patient's status will only be listed.

#### **14.7. Study Medication**

The number of patients at each study visit will be summarized by treatment group.

The compliance to study medication, as recorded in the CRF will also be summarized by treatment group.

## **14.8. Concomitant Therapy**

Concomitant medications (medications present while on study medication) will be recorded throughout the study and at early termination. These medications will be coded using the WHO-drug dictionary. The number of patients from the Safety sample using prior or concomitant medications will be categorized by the WHO-drug category and preferred term, and presented for each treatment group. In any given category (e.g., drug category) a patient will be counted only once.

## **14.9. Efficacy Data**

### **14.9.1. Efficacy Outcomes**

The efficacy outcomes consist of the following objective assessments:

- Polysomnography (PSG) including: LPS, WASO, TST and SE
- Digit Symbol Substitution Test (DSST)

And the following subjective assessments:

- Pre- and post-sleep questionnaires (Pre-SQ and PSQ)
- Visual Analog Mood Scale (VAS)
- Benzodiazepine Withdrawal Symptom Questionnaire (BWSQ)

#### **14.9.1.1. Primary Efficacy Outcome**

The primary efficacy variable is the average latency to persistent sleep (LPS) as measured by polysomnography (PSG) on Nights 1 and 8.

#### **14.9.1.2. Secondary Efficacy Outcomes**

The secondary efficacy variables are:

- the average WASO, TST and SE as measured by PSG on Nights 1 and 8.
- the average LPS, WASO, TST and SE as measured by PSG on Nights 22 and 29
- the LPS, WASO, TST and SE as measured by PSG on Nights 1, 8, 22 and 29
- rebound effects through the LPS, WASO, TST and SE as measured by PSG on Night 36
- subjective assessments such as: sleep quality, depth of sleep, sleep latency (sSL), total sleep time (sTST), daytime function and daytime alertness
- residual effects through DSST score and VAS score
- subjective withdrawal symptoms after 5 weeks of VEC-162 treatment as measured by the benzodiazepine withdrawal symptom questionnaire (BWSQ)
- contribution of a PER3 gene polymorphism on the primary and secondary efficacy endpoints.

#### **14.9.2. Efficacy Analysis**

Continuous variables will be analyzed parametrically using ANOVA or ANCOVA models, and categorical variables will be analyzed using the generalized Cochran-Mantel-Haenszel (CMH) test with (pooled) site as a stratum.

##### **14.9.2.1. General Data Analysis Considerations**

###### **Imputation of missing data**

For the average PSG parameter values calculated as an average over 2 nights (Night 1 and 8 or Nights 22 and 29), if one of the 2 nights entering in the calculation of the average value is missing, then it will be imputed using the non-missing night value, e.g. if Night 1 is missing then it will be imputed using the Night 8 value and if Night 8 is missing, it will be imputed using the Night 1 value. If both post-baseline values are missing then the average value for this PSG parameter will be imputed using the baseline value only (Baseline Observation Carried Forward - BOCF).

The observed data will otherwise be used in the analyses.

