### **7.3. Patient Withdrawal Criteria**

The term “discontinuation” refers to the patient’s premature withdrawal from the study before completing all scheduled evaluations.

Patients may be discontinued from the study for any of the following reasons:

- If in the Investigator’s judgment, continuation in the study may prove harmful to the patient. Such a decision may be precipitated by adverse events, including the occurrence of rash, changes in vital signs, physical examination, ECG, or laboratory tests. The Investigator will maintain autonomy in making medical/safety decisions regarding the patient’s continued participation in the trial. Clinically notable abnormalities in vital signs or laboratory tests are provided in [Appendices 21.2](#) and [21.1](#), respectively, to guide clinical focus regarding a patient’s continued participation.
- Noncompliance
- At the request of the patient.

Any time a patient discontinues from the study, the interactive voice response system (IVRS) should be notified.

Documented reason: It will be documented whether or not each patient completed the clinical study. If, for any patient, study treatment or observations were discontinued, the reason will be recorded (only 1 choice is acceptable) on the electronic case report form (electronic CRF). Acceptable reasons for a patient discontinuing participation in this clinical study are as follows:

1. protocol deviation (including noncompliance)
2. adverse event(s)(including abnormal laboratory values, abnormal test procedures, and pregnancy)
3. lost to follow-up
4. death
5. patient withdrew consent

6. unsatisfactory therapeutic effect
7. other (specify)

Patients who prematurely discontinue from the study (Early Termination) will undergo a complete safety assessment as detailed in the Schedule of Evaluation (see [Table 2](#)). Patients who discontinue because of an AE, abnormal laboratory value, or abnormal test result will be followed until resolution or for 30 days, whichever is less. If a patient elects to withdraw from the study, he/she will be informed that it is extremely important that the reason for discontinuation be reported and that all EOS assessments required by the protocol are performed.

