## 14.2. Sample Size and Accrual

The sample size is based on the average LPS computed via PSG assessments from nights 1 and 8. Based on a t-test to detect a 15 minute difference between VEC-162 treated patients and placebo patients, and assuming a common standard deviation of 30 minutes, a sample size of 86 patients per treatment arm is needed in order to have 90% power with a two-sided alpha of 0.05. The standard deviation is based on data found in literature. Considering a 1:1:1 randomization between VEC-162 20mg, VEC-162 50mg and placebo, and a 20% drop-out rate, a total of 324 patients (108 per arm) will be needed.

A re-estimation of the sample size will be done through an adjusted one-sample variance procedure. In this procedure, a blinded variance estimation is obtained by adjusting the one-sample variance of the pooled sample.

Let  $N$  and  $VAR$  be the respective preliminary sample size and variance originally estimated (as per above). Let  $N(s)$  and  $VAR(s)$  be the respective sample size and variance of the pooled blinded sample at this sample-size re-assessment look. Then according to Zucker et al. (13), the following estimation of the variance ( $VAR(adj)$ ) will be used to generate an adjusted sample size  $N(adj)$ ;

$$VAR(adj) = VAR(s) - N(s) D^2 / 2(2N(s)-1),$$

where  $D$  is equal to a 15 point change from baseline

$N(adj)$  will then be generated using a two-group t-test procedure with a 0.05 two-sided significance level and the variance  $VAR(adj)$ .

Since this sample size re-assessment is not intended to stop the trial early due to efficacy but only to provide a variance re-estimation and a sample size recalculation, then after the recruitment of the first  $n(s)$  patients,

- if  $N(adj) \leq N$ , then a further  $N-N(s)$  patients will have to be recruited until the initially planned sample size  $N$  is reached.
- Otherwise if  $N(adj) > N$ , then a further  $N(adj)-N(s)$  patients will have to be recruited.

As the procedure does not require unblinding of the treatment code during the ongoing trial nor produce any estimation of a treatment effect hypothesis testing, then no adjustment to control the nominal significance level is required.

The required sample size could also be adjusted if the drop-out rate differs from the estimated drop-out rate. This change would be made via a protocol amendment.

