###### **14.9.2.4. Analysis of the Secondary Endpoints**

The continuous secondary efficacy variables will be analyzed using a similar parametric model as the one used in the analysis of the primary efficacy variable, i.e. an ANCOVA model that includes main effects for treatment and (pooled) site, the baseline assessment as a covariate and the treatment-by-baseline interaction term to check the consistency of treatment differences across various baseline score levels.

Categorical secondary efficacy parameters will be analyzed using a CMH test stratifying by (pooled) site.

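### Single-night PSG endpoints at Nights 22 and 29 are analysed as observed cases without using leavers' Night 1 and 8 recordings, so drop-out related to earlier on-treatment sleep would bias them

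*Protocol*

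**What the plan says.** Protocol 14.9.1.2 lists as secondary efficacy variables "the LPS, WASO, TST and SE as measured by PSG on Nights 1, 8, 22 and 29". These serve secondary objective 3 (5.1.2), the effect on each evaluation night. The same list has the two-night averages and, separately, "rebound effects through the LPS, WASO, TST and SE as measured by PSG on Night 36".

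The missing-data rules in 14.9.2.1 concern only the averages over Nights 1 and 8 and over Nights 22 and 29. One missing night takes the value of the other. For two missing nights, "If both post-baseline values are missing then the average value for this PSG parameter will be imputed using the baseline value only". Everything else falls under one sentence: "The observed data will otherwise be used in the analyses".

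The model for continuous secondary variables (14.9.2.4) is "an ANCOVA model that includes main effects for treatment and (pooled) site, the baseline assessment as a covariate", plus a treatment-by-baseline term. It contains no night term and no earlier post-baseline night.

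Three other places bear on the point:

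- 14.9.2.5 allows BOCF or MMRM-based sensitivity analyses, but they are optional and confined to the primary variable.
- 7.3 accepts "unsatisfactory therapeutic effect" as a reason for discontinuing, and the early-termination list in 10.2.3 contains no PSG.
- 14.2 plans for "a 20% drop-out rate, a total of 324 patients (108 per arm) will be needed".

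**The concern.** A patient who stops after Night 8 remains in the Full Analysis Set but contributes nothing to the Night 22 or Night 29 comparison. The two PSG nights already recorded on treatment would say much about how that patient was sleeping, and the model ignores them. The comparison then describes patients who stayed, and it matches the dose effect on that night only if staying is unrelated to post-baseline sleep once treatment, site and baseline are accounted for. The protocol itself foresees discontinuation for lack of effect, so that condition cannot be taken for granted.

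At stake is how the night-by-night results and the over-time graphs (14.9.2.6) are read. If poor sleepers leave, and do so more on placebo, a constant drug effect will seem to shrink from Night 8 to Night 29. The Nights 22/29 average keeps leavers through BOCF while Night 22 and Night 29 taken singly exclude them, so the average and its own components describe different patients.

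**Working it through.** **1. The plan's own figures.** Inputs from 14.2: difference 15 minutes, SD 30, two-sided alpha 0.05, power 90%. The normal formula n = 2(z₀.₉₇₅ + z₀.₉₀)² × SD²/difference² = 2(1.960 + 1.282)² × 900/225 gives 85 per arm after rounding up. The exact t-test needs 85.03, so 86, as stated. Then 86/0.8 = 107.5, rounded up to 108, and 3 × 108 = 324. The plan reproduces. If all the planned drop-out falls after Night 8, about 108 − 86 = 22 patients per arm are missing from the later nights.

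**2. Where the bias comes from.** The observed-case ANCOVA estimates

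true effect + [mean baseline-adjusted residual of drug stayers − mean baseline-adjusted residual of placebo stayers].

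The bracket is zero if staying depends only on treatment, site or baseline. It is not zero in general if staying depends on Night 1 or 8 sleep, because those nights correlate with Night 29 beyond what baseline explains.

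**3. Size at Night 29, by large-sample simulation of one dose against placebo.** From the plan: a 15-minute effect (held constant over nights), SD 30 and 20% drop-out. Assumed, because the protocol gives no figures: normal LPS, equal correlation between nights of 0.3 to 0.7, and all drop-out after Night 8. The SD of 30 was used either per night or for the two-night average. In the latter case the per-night SD is 30/√((1+ρ)/2), that is 37.2, 34.6 and 32.5 at ρ = 0.3, 0.5 and 0.7. Ranges below span the correlations and the selection strengths tried. Entries are minutes of LPS reduction; the truth is 15.

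| Who leaves | Observed-case ANCOVA | Also using Nights 1 and 8 |
|---|---|---|
| Depends on baseline only | 14.9–15.1 | 14.9–15.1 |
| Poor sleepers, mild common tendency in all arms | 14.0–14.7 | 14.8–15.2 |
| The 20% worst sleepers on Night 8, all arms (deterministic extreme) | 13.4–13.6 | 14.8–15.2 |
| Same tendency, but 30% leave placebo and 10% drug | 13.8–14.1 | 15.1–15.2 |
| Poor sleepers on placebo, unrelated on drug, 20% each, moderate | 13.2–13.8 | 14.9–15.3 |
| The same, strong selection | 12.0–13.0 | 14.8–15.3 |
| Depends on the unobserved Night 29 value, same rule in both arms | 13.4–14.1 | 13.5–14.3 |
| Depends on the unobserved Night 29 value, differing by arm | 10.2–12.4 | 10.6–12.8 |

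The mild common case loses 15 − 14.7 = 0.3 to 15 − 14.0 = 1.0 minute. Leaving related to sleep mainly on placebo loses 15 − 14.1 = 0.9 to 15 − 12.0 = 3.0 minutes. Swapping the arms in the placebo-only rows reverses the sign.

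**4. With no true effect.** Placebo-only outcome-related leaving makes the drug look worse by 1.1 to 1.4 minutes if it depends on Nights 1 and 8, and by 2.7 to 4.8 minutes if it depends on Night 29 itself.

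**5. Scale.** The standard error of an unadjusted difference with SD 30 and 86 per arm is 30 × √(2/86) = 4.6 minutes. A bias of 1 minute is 1/4.6 = 0.22 standard errors; 3 minutes is 3/4.6 = 0.65.

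**The case against.** The strongest reply is that little depends on these analyses. Maintenance of effect has its own objective and endpoint, the Nights 22/29 average, which has an imputation rule that retains leavers. The primary average has one too. A reader might infer that the trial's evidence of persistence is biased by this sentence; the documents do not support that. What remains is objective 3 and the graphs, behind the gatekeeper in 14.1.1. This stands and keeps the point modest.

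The bias is also conditional. Lack of effect is one of seven discontinuation reasons, with no expected frequency, and the protocol gives no drop-out by arm, reason or time. The 20% inflates a sample size built for the Nights 1/8 average, so placing all of it after Night 8 is an assumption. The figures at the 3-minute end need strong selection on placebo alone. These limits stand too; they restrict the size, not the mechanism.

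A reader might extend the point to Night 36, which falls under the same sentence. Objective 6 concerns rebound on stopping after five weeks of drug. Someone who left after Night 8 never had that exposure, and predicting a withdrawal response from treated nights would not answer the question. None of the figures above covers Night 36.

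A reader might also think a repeated-measures model removes the problem. The last two table rows show that it does not when leaving depends on the unrecorded night itself.

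Finally, 14.1 lets the SAP change methods without an amendment. That makes the repair easy, but the protocol as written states the observed-data rule and does not leave it open.

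**Conclusion.** The point holds for the single-night PSG endpoints at Nights 22 and 29. The stated method discards relevant on-treatment data from leavers and is unbiased only if leaving is unrelated to post-baseline sleep given treatment, site and baseline. If leaving depends on earlier post-baseline sleep, the LPS effect at those nights is off by about 0.3 to 1 minute of 15 (2% to 7%) under mild selection common to the arms. It is off by about 1 to 3 minutes (7% to 20%) if selection is mainly on placebo. Both ranges rest on 20% drop-out all after Night 8, correlations of 0.3 to 0.7 and a constant effect. They were worked out for LPS only, and the mechanism carries over to WASO, TST and SE without a figure. The bias is towards no effect when poor sleepers on placebo leave more, and the reverse if poor responders leave the drug arms. This calls for a cheap improvement to secondary analyses; it does not threaten the primary result.

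**What to change.** For LPS, WASO, TST and SE, fit one MMRM per parameter directly to the observed Nights 1, 8, 22 and 29. Include treatment, night, treatment-by-night, pooled site, baseline and baseline-by-night, with unstructured covariance. Report each night's dose-versus-placebo contrast from this model and keep the observed-case ANCOVA as supportive. Add a sensitivity analysis that departs from missing at random, for example by shifting the later-night values of leavers by a range of amounts, by arm.

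Leave Night 36 out of this model. Analyse it separately in patients who reach the wash-out night, and state that the result applies to those patients.

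The cost is SAP wording and modest programming. It needs no new data or patients, MMRM is already named in 14.9.2.5, and 14.1 allows the change before database lock without an amendment. The downside is reliance on missing at random, which is a weaker assumption than the one the observed-case analysis needs.

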###### **14.9.2.2. Statement of the Null and Alternate Hypotheses**

Statistical analyses will be performed using two-sided test. A 0.05 significance level will be used in all tests of treatment differences. Test for interaction will utilize a 0.10 statistical significance level.

The type I error will be controlled via Fisher's protected least significant difference (LSD). Using this procedure, an overall test of the overall treatment effect will be conducted and pairwise comparisons will be examined only if the overall treatment is significant at the 0.05 alpha level. Pairwise comparisons will also be examined at the 0.05 significance level.

###### **14.9.2.3. Analysis of the Primary Endpoint**

The primary efficacy variable, i.e., average LPS value over Nights 1 and 8, will be analyzed using an ANCOVA model that includes main effects for treatment and (pooled) site, the baseline assessment as a covariate and the treatment-by-baseline interaction term to check the consistency of treatment differences across various baseline score levels.

If the data for the primary efficacy variable does not satisfy underlying assumptions of normality and homogeneity of variance, then a data transformation such as a Log transformation (base 10) or a Logit may be applied, or a non-parametric model may be used to analyze the data.

###### **14.9.2.4. Analysis of the Secondary Endpoints**

The continuous secondary efficacy variables will be analyzed using a similar parametric model as the one used in the analysis of the primary efficacy variable, i.e. an ANCOVA model that includes main effects for treatment and (pooled) site, the baseline assessment as a covariate and the treatment-by-baseline interaction term to check the consistency of treatment differences across various baseline score levels.

Categorical secondary efficacy parameters will be analyzed using a CMH test stratifying by (pooled) site.

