#### **Single-blind Placebo Lead-in Period**

Those patients who fulfill the preliminary inclusion/exclusion criteria will be asked to return to the sleep clinic approximately 2.5 hours prior to their scheduled bedtime for the placebo lead-in. The scheduled bedtime in the sleep clinic will be calculated as 8 hours prior to the patient's typical wake times during his/her normal work week. For example, the scheduled bedtime of a patient who normally wakes up to get ready and go to work at

6:00am will be 10:00pm. Once the scheduled bedtime is determined for a given patient, the same scheduled bedtime will be used for that patient throughout all the inpatient sleep episodes.

The single-blind placebo lead-in period consists of two consecutive nights at the sleep clinic followed by approximately 5 days of outpatient treatment. At the beginning of the placebo lead-in, the sleep diary data from the seven consecutive days immediately preceding Visit 2 will be reviewed to confirm eligibility. The patient must have completed the sleep diary for at least 4 days out of the seven. On the first night of the placebo lead-in period, instructions and a practice session should be given to the patient on how to properly complete the DSST and VAS. These first practice measurements will not be used in the analysis of this study. In addition, the patients will take a breathalyzer test and complete the pre-sleep questionnaire (Pre-SQ) each inpatient night. Patients will complete the Pre-SQ prior to receiving single-blind placebo capsules 30 minutes ( $\pm$  5 minutes) prior to lights off. Lights off should occur within 15 minutes of their scheduled bedtime.

PSG recordings will be conducted in each of the two consecutive nights of the single-blind placebo lead-in period. The first PSG will be a diagnostic PSG (dPSG) which will also be used to exclude patients with any other sleep disorder (e.g. sleep apnea). Patients will be awakened at the end of the 8-hour sleep episode and will be asked to complete a battery of tests 1 hour ( $\pm$  15 min) after awakening. The battery of tests includes the following assessments **in order**: PSQ, VAS and DSST. On the morning after the dPSG, patients will be released from the sleep clinic and reminded to return to the sleep clinic that evening for a repeat night of testing.

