**Day -5**

- Vital Signs (body temperature, respiratory rate, blood pressure, and pulse)
- Adverse event query
- Battery of tests (Post-sleep questionnaire, VAS, and DSST, in this order; one hour [ $\pm 15$  minutes] after awakening))
- Drug Dispensing for out-patient use (single-blind treatment)
- Dispense outpatient PSQ and instruct patient to complete prior to the next scheduled visit

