### **Benzodiazepine Withdrawal Symptom Questionnaire (BWSQ)**

The Tyrer Benzodiazepine Withdrawal Symptom Questionnaire is a self-reported questionnaire which records the main symptoms experienced during withdrawal from benzodiazepines in pharmacologically dependent patients. The questionnaire consists of 20 symptoms. Each symptom is rated from 0 to 2. The absence of a symptom is rated as 0. The presence of a symptom is rated as either 1 or 2, with 1 being moderate and 2 being severe. The maximum possible score is 40. There are two versions of the BWSQ. The first version (BWSQ-1) is a retrospective assessment of the most severe symptoms experienced at any time during the use of, or the withdrawal from benzodiazepines. The second version (BWSQ-2) assesses symptoms within the immediate past (2 weeks) and it is appropriate for evaluating the frequency of symptoms during withdrawal. This study will use BWSQ-2 which will be completed at Day 30 ( $\pm 2$  days) and Day 37 ( $\pm 2$  days) as part of the EOS assessments. The BWSQ will be given to patients before the battery of tests (approximately 1 hour after awakening).

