#### **14.1.1. General**

The primary efficacy variable is the average Latency to Persistent Sleep (LPS) computed via PSG assessments from nights 1 and 8. The primary null hypothesis to be tested is that there are no differences among the treatments.

Statistical analyses will be performed using two-sided test. A 0.05 significance level will be used in all tests of treatment differences. Test for interaction will utilize a 0.10 statistical significance level.

For the primary efficacy endpoint, the type I error will be controlled via Fisher's protected least significant difference (LSD). Using this procedure, an overall test of the treatment effect will be conducted and pairwise comparisons will be examined only if the overall treatment is significant at the 0.05 alpha level. Pairwise comparisons will also be examined at the 0.05 significance level.

In addition, for labeling purposes only, the experiment wise Type I error will be controlled to a maximum of 5%. A gatekeeper strategy will be employed such that any secondary endpoints will be considered for statistical significance only if the primary endpoint to be statistically significant.

Data will be summarized by treatment group (and by visit when applicable), with respect to demographic and baseline characteristics, efficacy variables, and safety variables.

Summary statistics will include the mean, N, standard deviation, median, minimum, and maximum values for continuous variables, and frequencies and percentages for categorical variables.

Continuous variables such as latency to persistent sleep (LPS), wake after sleep onset (WASO), total sleep time (TST) and sleep efficiency (SE) will be analyzed using an ANCOVA model with treatment and pooled center as main effects, baseline as a covariate and the treatment-by-baseline interaction. An exploratory analysis will be performed to explore whether there are treatment-by-center interactions. If a treatment-by-center interaction is detected, the interaction will be explored in an ad-hoc manner.

Categorical variables will be analyzed using Cochran-Mantel-Haenszel (CMH) test blocking on centers (or pooled centers).

Details of the model and the analyses will be specified in the SAP. All statistical analyses will be performed using SAS®, Version 8.2 or higher.

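### Any sleep-questionnaire item analysed as ordinal is tested by CMH stratified by site alone, leaving its scheduled lead-in rating unused and giving up some power

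*Protocol*

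**What the plan says.** Three places in the protocol set the method for categorical variables, and site is the only stratum in each:

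- Section 14.1.1: "Categorical variables will be analyzed using Cochran-Mantel-Haenszel (CMH) test blocking on centers (or pooled centers".
- Section 14.9.2: "categorical variables will be analyzed using the generalized Cochran-Mantel-Haenszel (CMH) test with (pooled) site as a stratum".
- Section 14.9.2.4: "Categorical secondary efficacy parameters will be analyzed using a CMH test stratifying by (pooled) site".

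For continuous secondary endpoints, Section 14.9.2.4 prescribes "an ANCOVA model that includes main effects for treatment and (pooled) site, the baseline assessment as a covariate", plus a treatment-by-baseline interaction.

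Questionnaire data are scheduled before randomization. On Day -6 and Day -5 (Section 10.1.2) patients complete the "Battery of tests (Post-sleep questionnaire, VAS, and DSST, in this order". Section 6.1.1 has them "complete the pre-sleep questionnaire (Pre-SQ) each inpatient night" during the lead-in. An outpatient PSQ is handed out on Day -5 and collected on Night 1.

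Section 14.9.1.2 lists as secondary variables "subjective assessments such as: sleep quality, depth of sleep, sleep latency (sSL), total sleep time (sTST), daytime function and daytime alertness". Neither that section nor Section 11.2 gives response scales for these items or says which are categorical. The only questionnaire whose items have stated graded categories is the BWSQ ("Each symptom is rated from 0 to 2"), and it is given on Days 30 and 37 only.

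**The concern.** The plan treats baseline adjustment as standard for one class of secondary endpoint and omits it for the other without giving a reason. A self-rated item is often correlated with the same patient's earlier rating. Where that is so, a comparison stratified by site alone leaves explainable between-patient variation in the error term.

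The stake is power for those parts of secondary objective 4 (Section 5.1.2) that turn out to be ordinal. Section 14.1.1 places secondary endpoints behind a gatekeeper for labeling, so they may carry claims. Section 14.2 sizes the trial on latency to persistent sleep (LPS) alone, and no power is stated for any subjective endpoint.

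**Working it through.** **The plan's own figure.** Section 14.2 gives a 15-minute difference, SD 30, two-sided alpha 0.05 and 90% power.

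- Normal approximation: n = 2 × (1.960 + 1.282)² × (30/15)² ≈ 84.1, so 85 per arm.
- Noncentral t: 86 per arm, with power 90.3%.
- Drop-out: 86/(1 − 0.20) = 107.5, so 108 per arm and 324 in total.

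The stated sample size reproduces. It concerns LPS and is not in question.

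**Analytic size of the loss.** Let ρ be the correlation of outcome with baseline. Adjustment multiplies the error variance, and so the required n, by 1 − ρ². For a test with 80% unadjusted power, adjusted power is Φ[(1.960 + 0.842)/√(1 − ρ²) − 1.960]. The documents give no ρ, so a range is shown.

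| Assumed ρ | n factor 1 − ρ² | Adjusted power |
|---|---|---|
| 0 | 1.00 | 80.0% |
| 0.3 | 0.91 | 83.6% |
| 0.5 | 0.75 | 89.9% |
| 0.7 | 0.51 | 97.5% |

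These are upper figures for an ordinal item, because cutting a scale into categories weakens the observed correlation.

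**Simulation with ordinal data.** From the protocol: 86 per arm, alpha 0.05 two-sided, and a latent shift of 15/30 = 0.5 SD borrowed from LPS. Assumed: four categories cut at the quartiles, 15 pooled sites, and ρ on the latent scale. There were 4,000 runs per setting, each a single pairwise comparison. Three tests were compared:

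- A: mean-score CMH by site, as the protocol's rule would give for an ordinal item.
- B: site-stratified CMH on category scores after regression on the baseline category.
- C: CMH by site crossed with dichotomized baseline.

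| Assumed ρ | A: site only | B: baseline-adjusted | C: baseline as extra stratum | B − A |
|---|---|---|---|---|
| 0 | 80.9% | 80.7% | 77.0% | −0.2 |
| 0.3 | 80.3% | 83.3% | 78.9% | 3.0 |
| 0.5 | 81.3% | 88.2% | 83.4% | 6.9 |
| 0.7 | 80.1% | 94.2% | 88.2% | 14.1 |

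The Monte Carlo standard error near 80% is √(0.8 × 0.2/4000) ≈ 0.6 points. Type I error was 4.3% to 5.4% across all three tests.

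Test C loses power at low correlation and stays below B throughout. Crossing 15 sites with two baseline levels gives 30 strata for 172 patients, about 172/30 ≈ 6 each.

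**Second set of assumptions.** With five categories, 9 pooled sites, 108 per arm (the randomized number, before drop-out), a 0.39 SD shift and adjustment on ranks, site-only power was 77%. Adjusted power was 80%, 85% and 89% at ρ = 0.3, 0.5 and 0.6, with type I error again about 5%. Direction and rough size agree.

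**The case against.** The strongest objection is that no affected endpoint is identified. Subjective sleep latency and total sleep time are naturally continuous, the digit symbol test is a count of correct items and the visual analog scale is a 100 mm line. All of these would fall under the baseline-adjusted ANCOVA. The BWSQ has no baseline. If every remaining Pre-SQ and PSQ item is also analysed as continuous, nothing is lost. This stands, and it makes the point conditional.

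A reader might infer that objective 4 as a whole is tested inefficiently, or that the analysis is biased. The documents support neither. The response scales are not given, and site-stratified CMH is valid in a randomized trial.

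A reader might also fault the generalized CMH because it could mean the general-association statistic, which ignores category order. The protocol does not fix the statistic, and Section 14.1.1 leaves model details to the SAP, so that is not a fault here. The stratification is different, because it is stated three times with site as the only factor.

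Section 14.6 does let baseline variables that differ at the 0.10 level be added to efficacy analyses. It therefore cannot be said that imbalance is ignored. That route is optional, depends on a baseline test and is labelled an exploratory sensitivity analysis, so the main analysis stays unadjusted.

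Three smaller objections also stand. A schedule does not guarantee a completed rating for every randomized patient. Selection on subjective latency, subjective sleep time and lead-in LPS (Section 7.1, criteria 6 to 8) may narrow the baseline range and weaken the correlation. At a correlation of 0.3 or below the gain is small.

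**Conclusion.** The point holds as an efficiency matter, limited to Pre-SQ and PSQ items analysed as ordinal that have a lead-in rating. From about 80% power, omitting baseline costs nothing at a correlation of 0, about 3 points at 0.3, about 7 at 0.5 and about 14 at 0.7. Those figures rest on an assumed correlation, number of sites, set of categories and effect, none of which the protocol gives for these items.

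Adjustment costs essentially nothing even if the baseline proves uninformative (80.7% against 80.9%, within simulation error) and needs no new data. It is a worthwhile improvement to secondary analyses rather than the correction of an error.

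**What to change.** In Sections 14.9.2 and 14.9.2.4, or in the SAP (Section 14.1 allows method changes before database lock without an amendment):

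- List which Pre-SQ and PSQ items are ordinal.
- Analyse those with a lead-in rating by rank ANCOVA stratified by pooled site: regress outcome ranks on baseline ranks, then apply the site-stratified CMH mean-score test to the residuals.
- Name one baseline rating per endpoint in advance, for example the inpatient lead-in PSQ for inpatient endpoints. State whether that is Day -6, Day -5 or their average.
- Do not add baseline as a further CMH stratum.
- Keep plain site-stratified CMH for variables without a baseline, including categorical BWSQ items.
- Give a rule for missing baseline ratings.

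The cost is wording, slightly more programming and that missing-baseline rule.
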